### Statistical methods

The principal analysis will examine the relationship between positive NIPS result and the follow-up outcome. Further subanalyses will also take into account the protocol stage at which arrhythmia was induced as well as the tachycardia cycle length and duration. At the first stage, groups of patients will be extracted by the occurrence of arrhythmic events during NIPS,- as in section 4. Afterwards, these groups will be compared according to the data collected during the follow-up (endpoints). The group, in which the endpoints occurred, will be compared with a group of patients without endpoints according to the NIPS result using Kaplan–Meier survival curves and tested with a log-rank test. A P value of 0.05 will be considered statistically significant for all analyses.

Next, with Multivariate Cox Proportional Hazards Model the presence or absence of the NIPS result correlation will be determined with other risk factors affecting the possibility of developing adequate ICD interventions that have been previously described in the available literature and widely accepted, that is, echocardiogram result, NYHA class, the presence of atrial fibrillation, renal function, width of native QRS complexes. The sensitivity, specificity, positive, and negative predictive value in predicting the occurrence of NIPS endpoints also will be calculated using Student’s t test or the Mann–Whitney test for continuous variables, where appropriate.

With the chi-square test, 150 patients have been estimated as needed for inclusion in the study. This assumption is based on the calculation that primary endpoints will occur in 6.7 % patients, and the result of NIPS will be abnormal in 30 % of those patients and in 7.9 % of patients without VT/VF recurrences [2, 30, 31]. This number of patients will be sufficient to demonstrate significant difference (*P* < 0.05) between the groups.

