### The aim of the study

The aim of the study is to evaluate the usefulness of NIPS in determining the likelihood of life-threatening arrhythmic events in patients with ICD.

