#### Outpatient follow-up

The follow-up will be conducted at the outpatient clinic for patients with ICD located in our center. Analysis of records of registered memory device classified as VT/VF episodes will be collected in printed and electronic versions for further investigation by the study team. Medical history will be taken, and a physical examination will be carried out. In case of endpoint VT/VF occurrence during follow-up, the time from NIPS test to ICD episode detection/therapy will be measured. The follow-up will last one year and will be conducted every 3 months; thus, each patient will have four visits – one at 3, 6, 9 and 12 months after performing NIPS. The following parameters will be collected:The patient’s clinical status will be determined on the basis of a physical examination, NYHA class, changes in medication, hospitalizations, cardiac events such as syncope, ICD discharges, palpitations and other, which occurred after the previous visit.The ICD memory will be examined, and all events will be analyzed. All ICD interventions will be analyzed and classified as appropriate or inappropriate. The type of cardiac rhythm (VF, VT, or other) and the cycle length and duration will be also measured.All follow-up visits and data collection will be performed by the principal investigator (PF). If necessary, drug therapy will be modified during follow-up, but the result of the NIPS will not be taken into account when changes in the antiarrhythmic drug therapy are considered. Changes in ICD programming will be possible; however, these will be based on arrhythmic events occurring during follow-up and not based on the results of the NIPS.

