### Expected results

During the NIPS the following clinical situations are expected to occur:lack of induction of arrhythmia (negative result)induction of ventricular extrasystoles (negative result)induction of hemodynamically stable nsVT (negative result)induction of hemodynamically unstable nsVT (positive result)sVT induction (positive result)VF induction (positive result).

It is expected that appropriate ICD interventions during follow-up will occur more often in patients who had sustained ventricular arrhythmias induced during NIPS (positive result). The primary endpoint of the follow-up will be appropriate intervention of ICD or sudden cardiac (arrhythmic) death; the secondary, appropriate ICD intervention or death from cardiovascular causes; and the tertiary, appropriate ICD intervention, death or hospitalization for cardiovascular causes. Because all patients will remain under the study follow-up for 1 year, the degree of exposure to arrhythmia recurrence (arrhythmia burden) will be determined defined as the number of relevant interventions during the year of observation.

Appropriate ICD intervention is defined as the high or low energy treatment due to the occurrence and detection of VT/VF.

For death from cardiovascular causes, it is considered death due to VF, extensive myocardial infarction, end-stage heart failure, or electromechanical dissociation or asystole due to presumed cardiovascular cause.

For sudden cardiac (arrhythmic) death, death due to sVT/VF or, in the absence of available documentation, death that occurred within 1 hour of the onset of symptoms [29] may be considered. Every effort will be made to interrogate ICD postmortem in order to establish the mode of death.

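### Kaplan–Meier curves for the primary and secondary endpoints can only censor deaths outside the endpoint, so the displayed one-year risk is biased slightly upward if such deaths occur; cumulative incidence curves would avoid this

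*Protocol article*

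**What the plan says.** The aim is "determining the likelihood of life-threatening arrhythmic events in patients with ICD". In Expected results, "The primary endpoint of the follow-up will be appropriate intervention of ICD or sudden cardiac (arrhythmic) death", and next comes "the secondary, appropriate ICD intervention or death from cardiovascular causes". The same section defines cardiovascular death: "it is considered death due to VF, extensive myocardial infarction, end-stage heart failure, or electromechanical dissociation or asystole due to presumed cardiovascular cause". Several of these causes are not arrhythmic, so a patient can die of them without ever meeting the primary endpoint.

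On follow-up, the Outpatient follow-up section states: "The follow-up will last one year and will be conducted every 3 months". Expected results bases its arrhythmia-burden measure on full follow-up: "Because all patients will remain under the study follow-up for 1 year". Death before one year is not discussed there.

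Statistical methods applies the curves and test ("using Kaplan–Meier survival curves and tested with a log-rank test") to the endpoints without distinguishing between them. I read this as curves by NIPS result. The section then names a Cox model, and also sensitivity, specificity and positive and negative predictive values. It names no competing-risk method, and it does not say how a death outside the endpoint enters the predictive values.

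**The concern.** A patient who dies of pump failure before any appropriate device therapy can no longer have the primary event. Censoring at death treats that patient as if the event could still happen later, at the rate seen in the survivors. One minus Kaplan–Meier then estimates risk in a setting where no one dies of anything else, and this is never lower than the proportion of tested patients who have the event. The secondary endpoint has the same feature, but only for non-cardiovascular deaths.

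The plan also reports predictive values on the same patients. On the ordinary reading, a patient who died of pump failure is event-free there and stays in the denominator. The curve at 12 months and the predictive value could then give two different one-year risks for one group. The stated aim concerns likelihood, and the Discussion foresees that positive patients may need more intensive treatment, so the absolute risk by NIPS result is likely to be read and used.

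**Working it through.** **Inputs from the article (Statistical methods).** 150 patients; primary endpoint in 6.7%; NIPS abnormal in 30% of patients with the event and in 7.9% of those without.

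**Planning table implied.** The article states no one-year risk by NIPS result, but its inputs give one.
- Events: 0.067 × 150 ≈ 10, leaving 140 without the event.
- NIPS-positive: 0.30 × 10 = 3 with the event and 0.079 × 140 ≈ 11 without, so 14 in all.
- NIPS-negative: 7 with the event and 129 without, so 136 in all.
- Risk: 3/14 = 21.43% (the planning positive predictive value) and 7/136 = 5.15% (one minus the negative predictive value, 129/136 = 94.9%).

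The adequacy of 150 patients is a separate matter and is not tested here.

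**The mechanism in whole patients.** Suppose k of the 14 NIPS-positive patients die outside the endpoint before all three events. With everyone else followed to 12 months, one minus Kaplan–Meier = 1 − (11 − k)/(14 − k).
- k = 0: 1 − 11/14 = 21.4%
- k = 1: 1 − 10/13 = 23.1%
- k = 2: 1 − 9/12 = 25.0%
- k = 3: 1 − 8/11 = 27.3%

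The proportion with the event stays 3/14 = 21.4% throughout. These are illustrations with the least favourable ordering. If every competing death came after the last event in the group, the curve would still read 21.4%.

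**The expected size.** The article gives no competing mortality, so a range of 2–15% in one year is assumed. Take the planning proportion as the true cumulative incidence c1, the assumed competing mortality as c2, and constant cause-specific hazards. Then

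h1 = −ln(1 − c1 − c2) × c1/(c1 + c2), and one minus Kaplan–Meier = 1 − exp(−h1).

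Worked line, NIPS-positive with c2 = 5%: −ln(1 − 0.2643) = 0.307; × 0.2143/0.2643 gives h1 = 0.249; 1 − exp(−0.249) = 22.0%.

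| Assumed c2 | All patients (true 6.7%) | NIPS-positive (true 21.43%) | NIPS-negative (true 5.15%) |
|---|---|---|---|
| 2% | 6.77% | 21.66% | 5.20% |
| 5% | 6.88% | 22.03% | 5.28% |
| 10% | 7.07% | 22.68% | 5.43% |
| 15% | 7.27% | 23.39% | 5.59% |

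The excess is about 0.1–0.6 points overall, 0.2–2.0 points in NIPS-positive and 0.05–0.4 points in NIPS-negative patients.

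**Against sampling error.** √[p(1 − p)/n] is 2.0 points overall (n = 150), 11.0 points for NIPS-positive (n = 14) and 1.9 points for NIPS-negative (n = 136). The bias is below the standard error in every cell.

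**The difference between groups.** The true planning difference is 21.43 − 5.15 = 16.28 points.
- Competing mortality 5% in both groups: 22.03 − 5.28 = 16.75 points. The ratio barely moves, from 4.16 to 4.17.
- 15% in NIPS-positive, 2% in NIPS-negative: 23.39 − 5.20 = 18.19 points.
- 2% in NIPS-positive, 15% in NIPS-negative: 21.66 − 5.59 = 16.07 points, below the true difference.

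The direction of the effect on the difference therefore depends on which group has the competing deaths.

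No planning rate is given for the secondary endpoint or for non-cardiovascular death, so no figure is offered there.

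**The case against.** The best defence has four parts.

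*The article does not say that these deaths are censored, and such rules often sit in an analysis plan.* The first half is true. But a Kaplan–Meier curve knows only event or censored, and counting these deaths as events would change the endpoint. An analysis plan could carry such patients to 12 months as event-free. With complete follow-up that gives the cumulative incidence, so it would be the remedy proposed here under another name. The point is about the method named, not about a missing detail.

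*The principal analysis is a test of association, and that test is sound.* This stands. A reader might infer that the log-rank or Cox result is invalid. It is not: censoring deaths outside the endpoint leaves both as proper comparisons of the cause-specific hazard.

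*The secondary endpoint already counts cardiovascular deaths, and the predictive values can supply absolute risk.* Both largely stand. The problem lies mainly with the primary endpoint. The predictive values give the right quantity if these deaths stay in the denominator, but the article does not say that they do.

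*The size is small.* This stands too. The larger illustrations (25.0%, 27.3%) need two or three of 14 patients to die outside the endpoint, all before any event. Nothing in the article supports that frequency.

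Two stronger readings also fail. A reader might infer that the curves must exaggerate the separation between groups; the last calculation shows that the difference can also shrink. A reader might infer that curve and predictive value are bound to disagree. That needs at least one competing death before a later event in the same NIPS group, together with a predictive value that counts that patient as event-free.

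**Conclusion.** The concern holds as a modest one about displayed absolute risk. For endpoints that leave out some deaths, one minus Kaplan–Meier is the wrong estimator of the one-year risk in tested patients, and its error can only be upward. Under the planning proportions and an assumed 2–15% competing mortality, it would read about 21.7–23.4% instead of 21.4% in NIPS-positive and 5.2–5.6% instead of 5.1% in NIPS-negative patients. This rests on constant hazards, on complete one-year follow-up apart from death, and on a mortality range that the article does not supply. The bias is below sampling error, and the principal test, its P value and the Cox hazard ratios are unaffected. It is worth correcting because it is systematic, because confidence intervals do not cover it, and because it can set the curve against the predictive values in the same paper.

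**What to change.** In Statistical methods:

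- For the primary and secondary endpoints, display Aalen–Johansen cumulative incidence curves by NIPS result. The competing event is non-arrhythmic death for the primary endpoint and non-cardiovascular death for the secondary.
- Keep the log-rank test and the Cox model, and describe them as cause-specific comparisons.
- State that a patient who dies outside the endpoint without a prior event counts as event-free in the predictive values. With complete follow-up, the 12-month readings then equal the positive predictive value and one minus the negative predictive value.

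The cost is a sentence or two of text and one more standard analysis. No new data are needed, since deaths and their causes must already be classified for the endpoints. The only visible consequence is that the reported risks will be slightly lower if competing deaths occur.

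### The protocol calls 150 patients sufficient without stating a power; on its own inputs the power is only about 57–59%

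*Protocol article*

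**What the plan says.** The sample size paragraph closes the Statistical methods section of the protocol article. It states: "With the chi-square test, 150 patients have been estimated as needed for inclusion in the study". The inputs are that "primary endpoints will occur in 6.7 % patients", that "the result of NIPS will be abnormal in 30 % of those patients", and that it will be abnormal "in 7.9 % of patients without VT/VF recurrences". The conclusion drawn is: "This number of patients will be sufficient to demonstrate significant difference", with P < 0.05 in brackets. The same section sets the level: "A P value of 0.05 will be considered statistically significant for all analyses".

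The article gives no power, does not say whether the test is one- or two-sided, and does not say whether the chi-square test is continuity-corrected. The relationship between a positive NIPS result and outcome is named as the principal analysis, to be tested by log-rank. Follow-up is one year, and the Expected results section takes it that every patient will complete it.

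**The concern.** All the numbers needed to check the conclusion are printed beside it, and it does not follow from them. An endpoint rate of 6.7% in 150 patients leaves about 10 patients with events. The comparison turns on how many of those 10 had an abnormal NIPS result, and a shift of one patient decides significance.

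What is at stake is how the result will be read. The Discussion says that NIPS-positive patients may need more intensive treatment, and the Limitations section presents this and similar studies as the way to learn whether NIPS results can guide medication and device programming. A reader told in advance that the size was adequate has grounds to take a non-significant result as evidence against NIPS. With about 10 events, such a result would be a likely outcome even if the assumed association were true.

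**Working it through.** **Inputs**, all from Statistical methods: N = 150; endpoint rate 0.067; NIPS abnormal in p1 = 0.30 of patients with the endpoint and p2 = 0.079 of those without; significance level 0.05. Assumed: two-sided test, no continuity correction, no loss to follow-up. The last two favour the plan.

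**Step 1. The expected table.** 150 × 0.067 = 10.05, so about 10 patients with events and 140 without. 0.30 × 10 = 3 and 0.079 × 140 = 11.06. The expected result is 3/10 against 11/140.

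**Step 2. The plan's own claim.** For 3/10 against 11/140, the pooled proportion is 14/150 = 0.0933 and

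z = (0.3000 − 0.0786) / √[0.0933 × 0.9067 × (1/10 + 1/140)] = 0.2214 / 0.0952 = 2.33,

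so chi-square = 5.41 and P = 0.020. If the data fall exactly on the planning values, the uncorrected test is significant. That is not power.

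**Step 3. Power by the normal approximation.** The pooled proportion is (3 + 11.06)/150 = 0.0937.

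- Standard error under no difference: √[0.0937 × 0.9063 × (1/10 + 1/140)] = 0.0954
- Standard error under the planning values: √[0.30 × 0.70/10 + 0.079 × 0.921/140] = 0.1467
- Power = Φ[(0.221 − 1.96 × 0.0954)/0.1467] = Φ(0.232) = 59.2%

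**Step 4. Exact power.** Summing the binomial probabilities of every table with 10 and 140 patients that gives P < 0.05 by the uncorrected chi-square yields 57.5%. Letting the number of events vary as Binomial(150, 0.067) gives 57.2%.

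The reason is visible by hand. With a true rate of 30%, the chance of two or fewer NIPS-positive patients among 10 events is 38%, and 2/10 against 11/140 gives P = 0.19.

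**Step 5. The planned log-rank test.** The inputs imply that 0.067 × 0.30 + 0.933 × 0.079 = 9.4% of patients are NIPS-positive, about 14 of 150. One-year risk is 0.0201/0.0938 = 21.4% in NIPS-positive and 0.0469/0.9062 = 5.2% in NIPS-negative patients, a hazard ratio of ln(1 − 0.214)/ln(1 − 0.052) ≈ 4.5. With exponential event times, one year of complete follow-up and 20,000 simulated studies, log-rank power is about 59%.

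**Step 6. Size for a conventional target.** With r = 0.933/0.067 = 13.9 patients without events per patient with one, pooled proportion 0.0938 and 80% power:

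n1 = [1.96 √(0.0938 × 0.9062 × (1 + 1/r)) + 0.842 √(0.30 × 0.70 + 0.079 × 0.921/r)]² / 0.221² = (0.592 + 0.390)² / 0.0488 = 19.7, so 20 events.

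20 × 14.9 ≈ 299 patients. Exact power at 20 against 279 is 80.4%, and simulated log-rank power at 299 is 80.3%. For 90% power the formula gives 433.

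**Step 7. Other settings.** A one-sided uncorrected test at 0.05 gives 67% at 150 patients, the highest of any variant tried at the 10:140 split.

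**The case against.** **The plan promises no particular power, so nothing is contradicted.** Read literally, the paragraph may say only that the expected table is significant, and by the uncorrected chi-square it is (P = 0.020). This limits how the point can be put. The 80% and 90% benchmarks are conventions brought from outside. It does not rescue the sentence, because a design that misses its own assumed effect about 4 times in 10 is not sufficient to demonstrate it. A full protocol might state a power, but that would not change what these inputs deliver.

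**The chi-square test is unsuitable and power is really 43–47%.** A reader might infer this, since the smallest expected cell is 10 × 14/150 = 0.93 and the expected table gives P = 0.078 with Yates' correction and P = 0.053 with Fisher's test. The inference does not hold. At 10 against 140 with a common rate of 14/150, the uncorrected chi-square has a true type I error of 4.1%, so it is not anti-conservative. Yates and Fisher run at 1.7% and 2.1%. Their lower power (43.2% and 46.9%) reflects that conservatism, and the article names neither.

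**Sizing by chi-square while analysing by log-rank is a defect.** It has no consequence here. Follow-up is fixed at one year, the two tests have nearly the same power, and the simulated log-rank type I error is about 5%.

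**The planners took the expected P value for power.** The inputs fit that account (6.7% is 10/150 and 7.9% is 11/140), but the document does not say so. Another route also comes close: two equal groups at 90% power, two-sided and continuity-corrected, need 73 each, or 146. That contradicts the 6.7% endpoint rate, so it does not justify 150, but it shows that the origin of the figure is unknown.

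**Low power harms no one in the study.** It is true that the Outpatient follow-up section keeps NIPS results out of decisions on antiarrhythmic drugs and device programming. The consequence lies in how the result is interpreted.

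**Conclusion.** The point stands in a limited form. The protocol asserts that the size is sufficient, states no power, and gives inputs that yield about 57–59% two-sided power for the tests it names. An 80% target would need about 299 patients, roughly twice the planned number.

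This rests on the plan's own three rates, a two-sided 0.05 level, an uncorrected chi-square test, complete follow-up and, for the log-rank figure, exponential event times. Any loss to follow-up would tend to lower the power. A one-sided test would raise it only to 67%.

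The documents do not support going further. They do not show that the planned tests are invalid or how 150 was reached. Nor do they say that a null result will be read as absence of prognostic value; that is a risk which the present wording leaves open, not a stated intention.

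**What to change.** Replace the sentence that calls the number sufficient with a statement of the actual power, for example:

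> With 150 patients and about 10 primary events, power to detect the assumed difference is about 57–59% (two-sided 0.05). A non-significant result will not be taken as evidence that NIPS lacks prognostic value, and the hazard ratio will be reported with its 95% confidence interval.

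This is a wording change. Enrolment and the planned tests need not change, and there is no case for requiring Fisher's test or a permutation log-rank test: the first would lower power from about 57% to 47% without correcting any type I inflation, and the ordinary log-rank test is already close to its nominal level. The only cost is a less favourable stated figure.

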## Discussion

This study will provide information regarding the result of NIPS on the occurrence of life-threatening arrhythmic events in patients with ICD. It is expected that appropriate ICD interventions during follow-up will occur more often in patients who had sustained ventricular arrhythmias induced during NIPS. Consequently, these patients may require more aggressive antiarrhythmic therapy or prophylactic ablation of arrhythmia substrate to prevent the occurrence of arrhythmias and ICD discharges.

### Limitations

The study has some limitations. First, although all consecutive patients attending our outpatient clinic will be invited to the study, probably not all will give consent to enter the trial. Thus, the study group will consist of all consecutive patients who agreed to participate in the study but not of all our patients with ICD. However, a logbook including all ICD patients will be maintained, so we will know exactly what percentage of our ICD patients entered the study. Secondly, the physician performing follow-up visits will not be blinded to the results of NIPS. However, as a rule, medication or ICD programming will not be influenced by NIPS results because there are no data indicating that this should be done. It is our and similar studies which should shed more light on this issue and answer the question whether NIPS results can be taken into account when medication and ICD programming changes are concerned.

